3.1 Inclusion Criteria

(1) Meets the diagnostic criteria for Chronic Pelvic Pain Syndrome (CPPS) according to the European Association of Urology (EAU) guidelines (2022 edition).

(2) Age: 18-70 years old;

(3) Can be clearly diagnosed as Generalized Anxiety Disorder or Major Depressive Disorder according to DSM-5 criteria;

(4) No significant pathological changes were observed in the physical examination and auxiliary examinations;

(5) No other treatments except for oral medications within 3 months prior to the visit;

(6) The patient is informed and voluntarily participates in the study.

3.2 Exclusion Criteria

(1) Patients with acute systemic and intracranial hemorrhagic diseases.

Individuals with severe underlying health conditions, such as cardiovascular, liver, kidney, respiratory, and blood diseases, as well as malignant tumors and other progressive diseases.

(3) Patients with cardiac metal membranes, cardiac pacemakers, intracranial metal implants, lumbar metal implants, and implantable electronic devices.

(4) Individuals with infections in the head or sacral region.

(5) Individuals exhibiting unstable vital signs.

(6) Patients who have had adverse reactions to magnetic therapy.

Individuals with atypical autonomic reflexes.

(8) Patients with cognitive impairments who cannot cooperate.

(9) Pregnant or breastfeeding women.

(10) Patients with a history of diseases that lead to peripheral nerve damage.

(11) Patients with serious illnesses, such as malignant effusion, active tuberculosis, cancer, or myasthenia gravis.

(12) Patients with severe mental illness or epilepsy.

3.3 Exit Standards

Participants will be asked to withdraw from the RCT under the following circumstances:

(1) If the patient does not adhere to the prescribed treatment plan or receives alternative treatment;

(2) If the patient experiences severe adverse reactions or changes in their condition that prevent them from continuing to participate in the trial;

(3) If the patient experiences significant organ dysfunction, unstable blood pressure, abnormal heart rate, or difficulty breathing;

(4) If the patient requests to withdraw informed consent due to intolerable adverse reactions or for no specific reason;

(5) If the patient loses follow-up during treatment or follow-up.

4. Plan Design

This study employs a prospective, randomized, blind, controlled trial design.

5. Sample Size Estimation and Grouping

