10.4 Expected Number of Recruits

66 patients with chronic pelvic pain syndrome accompanied by mental and psychological disorders who meet the selection criteria.

10.5 Time of participation in the study (duration of each participation and total time)

Participants who have been enrolled and received the first week of treatment (5 sessions) are considered to have participated in the study for the first time; participants receive 5 treatments per week for a total of 4 weeks (20 sessions); after the treatment course ends, they return to the hospital 8 weeks later for further examinations and assessments; the total duration of participation in the study ends 8 weeks after the treatment course concludes.

11. Data Management and Statistical Analysis Plan

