11.1.2 Case Report Form (CRF)

In clinical trials, it is necessary to record the specified observations or examination items in the case report form. The case report form includes...

The content must be completely consistent with the original data, and the basis for the results calculated from the original data should be traceable.

When filling out, you must meet the following standards:

(1) Fill in with a black signature pen or black ballpoint pen;

(2) Cases that have already signed the informed consent form and meet the inclusion criteria should fill out the case report form, even if they have not received treatment or are determined to not meet the inclusion criteria after treatment.

(3) When making corrections, the original record must be crossed out with a line (correction fluid or similar cannot be used), but the original record must remain legible. Additionally, the person making the correction must sign at the correction point and indicate the date of the correction.

(4) For unexamined items, it must be marked as "ND (Not Done)".

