11.2 Statistical Analysis

11.2.1 Analysis of Population Definition:

The patients who were enrolled and received treatment constitute the intention-to-treat population (ITT) for this trial. The population and the patients who comply with the requirements of this clinical trial protocol and complete this study constitute the per protocol population (PP). The statistical analysis will use intention-to-treat (ITT) for missing data, comparing the "full analysis set (FAS)" and the "per protocol set (PP)."

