11.2.2 Statistical Analysis Methods

Statistical analysis will be conducted using SPSS 27.0 software. Continuous data will be presented as mean ± standard deviation. Paired t-tests will be used for inter-group comparisons, and repeated measures ANOVA will be used for intra-group comparisons, including before and after treatment and during follow-up. Statistical significance will be indicated by a P value < 0.05. If there is a reduction in personnel during the trial, an intention-to-treat (ITT) analysis will be performed, comparing the "full analysis set (FAS)" and the "per-protocol set (PP)."

12. Data Confidentiality Plan

Participation in the trial and personal information during the trial are confidential. Information that can identify the subjects will not be disclosed to anyone outside the research team unless permission is obtained from the subjects. All research members and sponsors are required to keep the identities of the subjects confidential. The subjects' files will be stored in a locked filing cabinet and will only be accessible to researchers. To ensure that the research is conducted according to regulations, government regulatory agencies or members of the ethics review committee may review the subjects' personal information at the research site as necessary. When the results of this study are published, no personal information about the subjects will be disclosed.

13. Ethical Requirements and Informed Consent

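### The exit rule takes patients out of the trial, not only off stimulation, and ITT is limited to treated patients and used as a missing-data method, so a full intention-to-treat comparison is not possible as written

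*Protocol*

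**What the plan says.** Section 3.3 of the protocol, repeated in the Plan Summary, opens: "Participants will be asked to withdraw from the RCT under the following circumstances". The first trigger is "If the patient does not adhere to the prescribed treatment plan or receives alternative treatment". The second is "If the patient experiences severe adverse reactions or changes in their condition that prevent them from continuing to participate in the trial". The consequence named is leaving the RCT; stopping stimulation while staying under observation is not offered as a separate status.

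Section 11.2.1 defines the main population: "The patients who were enrolled and received treatment constitute the intention-to-treat population (ITT) for this trial". It continues: "The statistical analysis will use intention-to-treat (ITT) for missing data". Section 11.2.2 adds: "If there is a reduction in personnel during the trial, an intention-to-treat (ITT) analysis will be performed", with a full analysis set and a per-protocol set to be compared.

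Section 11.1.2 requires a case report form for consented patients who meet the inclusion criteria, "even if they have not received treatment or are determined to not meet the inclusion criteria after treatment". Section 5.2 lets patients who discontinue keep their number. Section 7 and Appendix 2 schedule the scores at t0, after each of four treatment weeks (t1 to t4), and 8 weeks after the course (t5). Section 6.5 allows oral medication during the study and asks patients to report significant changes.

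**The concern.** An intention-to-treat comparison needs two things: every randomised patient kept in the assigned group, and outcomes sought whatever happens to treatment. Section 11.2.1 gives up the first for patients who never start. Section 3.3 gives up the second for patients who stop adhering, turn to other treatment, or change in condition.

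These triggers are plausibly tied to outcome, and they may not be equal across arms. Sections 6.1 and 6.2 position active stimulation by a felt contraction, whereas the sham coil in 6.4 gives sound without a magnetic field. Patients on sham with continuing pain may guess their arm and look elsewhere; patients on active stimulation may exit for tolerability. Both are inferences from the design, not statements in the protocol.

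At stake is the primary comparison. Whether scores are collected after exit is a matter of trial conduct, so a later analysis plan cannot recover them.

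**Working it through.** **1. What happens to a patient who stops adhering in week 2.** Section 3.3 asks the patient to leave the RCT. The patient was treated, so 11.2.1 keeps the patient in ITT, with t0 and t1 scores. No section asks for t2 to t5 scores. Section 11.2.1 answers the gap with ITT, which says who is analysed and how they are grouped, not what value a missing score takes.

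**2. What happens to a patient randomised but never treated.** Section 11.1.2 requires a case report form, but 11.2.1 leaves the patient out of ITT.

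**3. The plan's own sample size.** Inputs from section 5.1: α = 0.05, β = 0.1, effect size 0.5, three groups. One-way ANOVA, noncentral F with λ = N·f² and f = 0.5, gives power 0.8823 at N = 51 and 0.9016 at N = 54, so 54 is reproduced. Enrolling 66 leaves room to lose 12 (12/66 = 18.2%). If all 66 are followed and analysed, power is 0.9535. Keeping exited patients needs no larger sample.

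**4. Possible bias (exit rates assumed; the protocol gives none by arm).** Let outcome Y be standard normal, with higher values worse. Let exit depend on L = ρY + √(1−ρ²)·E, with E independent standard normal, and let the fraction q with the highest L leave one arm. The mean of those remaining shifts by −ρ·φ(z₁₋q)/(1−q).

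- q = 0.10: φ(z)/(1−q) = 0.195. Times ρ = 0.3, 0.5, 0.7: 0.058, 0.097, 0.136 SD.
- q = 0.20: φ(z)/(1−q) = 0.350. Times ρ = 0.3, 0.5, 0.7: 0.105, 0.175, 0.245 SD.
- ρ = 1 (exit wholly determined by outcome) gives the upper bound, 0.195 and 0.350 SD.

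**5. Type I error.** Simulation with no true difference, 22 per arm, one-way ANOVA on patients remaining, 4,000 runs (Monte Carlo standard error near 5%: √(0.05×0.95/4000) = 0.0034). Exits are rounded to whole patients.

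| Exit in sham | Exit in each active arm | ρ | Type I error |
|---|---|---|---|
| 0 | 0 | 0.5 | 4.8% |
| 10% (2 of 22) | 10% (2 of 22) | 0.5 | 5.2% |
| 20% (4 of 22) | 5% (1 of 22) | 0.5 / 0.7 | 6.7% / 7.7% |
| 30% (7 of 22) | 5% (1 of 22) | 0.5 / 0.7 | 9.8% / 14.7% |

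Worse-off patients leaving sham makes sham look better and hides benefit. The same exits from an active arm would flatter that arm.

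**The case against.** The best defence is that early leavers are not lost altogether. They usually have baseline and weekly scores, and a likelihood-based model could use these under a missing-at-random assumption. Appendix 2 also lists an analysis of missing items and non-respondents at t5, and choosing a model or sensitivity analysis is commonly left to a SAP, which is not shown. This stands in part. The absence of a named model is not the point, and some analysis of treated patients is feasible. But Appendix 2 names no method, missing-at-random is least secure when exit follows treatment failure, and the ITT definition and missing-data sentence are not gaps: they are stated, and stated wrongly. That collection ends at exit is inferred from the words on leaving the RCT; no section says otherwise, and the phone and written contacts in section 7(4) are not extended to exited patients.

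Three stronger readings are tempting but unsupported.

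- A reader might take section 10.5, "Participants who have been enrolled and received the first week of treatment (5 sessions) are considered to have participated in the study", as excluding anyone who leaves in week 1. The sentence goes on to speak of a first participation, under a heading on participation time. It defines no analysis set.
- A reader might infer that the FAS and per-protocol sets lack the same patients, so that comparing them is empty. A treated patient who exits in week 2 is in ITT but not in per-protocol. What the sets share is the absence of scores after exit.
- A reader might divide the upper bound by 0.5 SD and conclude that most of the effect could be hidden. That assumes perfect dependence and exit in one arm only. Moreover, the protocol's 0.5 reproduces N = 54 as Cohen's f across three groups, not as a difference of 0.5 SD between two arms.

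Continuing every assessment would also be too much: the schedule includes rectal-electrode EMG and evoked potentials, and testing after a safety exit is a clinical matter.

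**Conclusion.** The point holds in a bounded form. Section 3.3 merges stopping treatment with leaving the trial, and 11.2.1 misdefines ITT and misuses it as a missing-data method. A full intention-to-treat comparison of all randomised patients is not possible under these rules.

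Bias is a risk, not a certainty. It needs exit that is both related to outcome and unequal between arms, and it can go either way. On the assumed rates, the shift in one arm's mean is small to moderate over the range shown, with 0.19 to 0.35 SD as an upper bound that should not be quoted as an expectation. With 22 per arm, 10% to 20% exit is only two to four patients.

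Loss of scores after exit is the larger problem. Restricting ITT to treated patients matters less if few randomised patients never start. The correction should be made because scores that are never collected cannot be restored at analysis.

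**What to change.** 1. Section 3.3 and the Plan Summary: leave the treatment-stopping rules unchanged, but state that stopping study treatment is not leaving the study. Unless consent is withdrawn, continue the scheduled questionnaires (pelvic pain scale or NIH-CPSI, DASS-21, SF-36) to t5, using the phone or written contact of section 7(4) where a visit is not possible. Do not require EMG or evoked-potential tests after a safety exit.
2. Section 11.2.1: define ITT as all randomised patients, analysed in the assigned group.
3. Sections 11.2.1 and 11.2.2: replace the sentence that uses ITT for missing data with an analysis of all available visits, for example a mixed model, plus one sensitivity analysis assuming worse outcomes after discontinuation.
4. Reconcile the other-treatment trigger in 3.3 with the oral medication that 6.5 allows, so that it is clear which changes count.

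Cost: protocol and consent wording, ethics approval, and renewed consent from patients still in the trial under section 13.3. Extra follow-up is a few contacts each for about 7 patients at the protocol's own 10% dropout (66 × 0.10 = 6.6), or 12 if the whole margin between 66 and 54 were used. No increase in sample size is needed.

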5.1 Sample Size Estimation

According to the research by Yang Jing-ming and his colleagues, under the conditions of β=0.1 and α=0.05, the effect size is 0.5. Pain scores will be used as the primary measurement standard, and G*Power 3.1.9.7 will be used to estimate the sample size. It is calculated that there will be approximately 54 patients in the study cohort, and considering a 10% dropout rate, each group will include 22 people, requiring a total of 66 participants for this RCT.

5.2 Patient Number and Randomization Group

Input patient data into the computer to obtain a subject number. All subject numbers will be three digits long, and patients will consistently use this number throughout the study, which will not be reassigned. Patients who withdraw their informed consent or discontinue the study after their patient number has been assigned will retain their initial number. Randomization will be conducted using a stratified block randomization method, stratified by gender, followed by block randomization within each stratum. Since the purpose of this study is to compare the improvement in symptom scores of chronic pelvic pain as well as anxiety and depression scores, gender is an important influencing factor. Therefore, gender will be used as a stratification factor, and block randomization (with 2 blocks per stratum and a block length of 4) will be employed for grouping. The aforementioned stratified block randomization can be implemented using SPSS software.

6. Research steps or treatment plan

6.1 Clinical intervention measures and steps.

(1) Before treatment: Conduct three examinations and seven comparisons. Researchers will carry out a risk assessment.

(2) Stimulation plan: First conduct rPMS, then conduct rTMS.

(3) Stimulation Site: For peripheral stimulation, the center of the circular coil will be aligned with the S3 region. During the stimulation process, if you feel contractions in the perineal muscles and dorsiflexion responses in the feet, it indicates that the position is correct. For central stimulation, the left DLPFC (l-DLPFC) region will be targeted for patients with major depressive disorder, while the right DLPFC (r-DLPFC) region will be targeted for patients with generalized anxiety disorder.

(4) Stimulation intensity: For peripheral stimulation, 50% of the maximum stimulation intensity will be applied. For central stimulation, the setting will be adjusted to 120% of the resting motor threshold (RMT).

(5) Stimulation parameters: ① Peripheral stimulation: 20 Hz, 2 seconds of stimulation, 28 seconds interval, a total of 1600 pulses. ② r-DLPFC: 1 Hz, 10 seconds of stimulation, 2 seconds interval, a total of 1000 pulses. ③ l-DLPFC: 10 Hz, 4 seconds of stimulation, 26 seconds interval, a total of 3000 pulses.

(6) End of stimulation: The stimulation coil will be moved away from the patient's stimulation site. The patient will be informed that the treatment is complete, and the evaluator will ask if there is any discomfort. If the patient is lying down, they will be instructed to gradually sit up and then stand to avoid falling.

(7) Treatment process: Once a day, 5 days a week, for a total of 4 weeks (20 sessions). The treatment course ends after the 20th session.

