**Appendix 7 Table 6 Randomization Application Form**

Application Date: Year Month Day Random Number:

| **General Information** | | | |
| --- | --- | --- | --- |
| Name Abbreviation: | | Age: years | Gender: Male □ Female □ |
| Weight： Kg | | Height： m | BMI Index： Kg/m2 |
| DMS-5 Diagnosis | Generalized Anxiety Disorder Severity: Mild □, Moderate □, Severe □ | | |
|  | Severity of Major Depression: Mild □, Moderate □, Severe □ | | |

| Selection Criteria Checklist | | |
| --- | --- | --- |
| Inclusion criteria | Yes | No |
| 1.Meeting the CPPS diagnostic criteria in the 2022 EAU guidelines | □ | □ |
| 2. Definitive generalized anxiety disorder or major depressive disorder | □ | □ |
| 3. Individuals aged between 18 and 70 years | □ | □ |
| 4.No identifiable pathological changes in physical examinations and auxiliary tests | □ | □ |
| 5.No treatment other than oral medications in the 3 months prior to the visit | □ | □ |
| 6.Patient's informed consent and voluntary participation in the study | □ | □ |
| All of the above criteria must be "yes," otherwise the patient cannot be enrolled. | | |

| Exclusion Criteria Checklist | | |
| --- | --- | --- |
| Exclusion criteria | Yes | No |
| 1. Patients in the acute phase of systemic and intracranial hemorrhagic diseases | □ | □ |
| 2.Individuals with serious underlying conditions, such as cardiovascular, liver, kidney, respiratory, and blood disorders, in addition to malignant tumors and other advancing illnesses | □ | □ |
| 3.Patients with cardiac metal membranes, cardiac pacemakers, intracranial metal implants, lumbar sacral metal implants, and implantable electronic devices | □ | □ |
| 4.Individuals with infections in the head or lumbar sacral regions | □ | □ |
| 5.Individuals exhibiting unstable vital signs | □ | □ |
| 6.Patients with previous adverse reactions to magnetic therapy | □ | □ |
| 7.Individuals with atypical autonomic reflexes | □ | □ |
| 8. Patients with cognitive impairment who cannot cooperate | □ | □ |
| 9. Expectant or breastfeeding women | □ | □ |
| 10. Patients with a history diseases causing peripheral nerve damage | □ | □ |
| 11. Patients with debilitating diseases, such as malignant effusion, active pulmonary tuberculosis, cancer, or myasthenia gravis | □ | □ |
| 12.Patients with severe mental illness or epilepsy | □ | □ |
| All of the above criteria must be "no"; otherwise, the patient cannot be enrolled. | | |

Is it eligible for enrollment: Yes □ No □

Reason for not enrolling:

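### Diagnosis selects the rTMS regimen and is recorded before allocation, but the stated analysis does not use it, and a patient with both diagnoses falls under two conflicting target rules

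*Protocol*

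**What the plan says.** **Treatment.** Section 6.1 items (3) and (5), Section 6.2 and the treatment plan in the Plan Summary tie the cortical target to diagnosis. MDD goes to the left DLPFC with "10 Hz, 4 seconds of stimulation, 26 seconds interval, a total of 3000 pulses". GAD goes to the right DLPFC at 1 Hz with 1000 pulses. Side, frequency and pulse count all differ. The peripheral arm receives rPMS only (Section 6.3). The sham arm follows the dual-target procedure with a coil that produces no field (Section 6.4).

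**Randomisation.** Section 5.2 states that "gender will be used as a stratification factor", because gender is thought to influence the pain, anxiety and depression scores. No second factor is named.

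**Recording.** The Appendix 7 form has one severity line for GAD and a separate one for MDD ("Severity of Major Depression: Mild" and so on). Both stand above the box for the randomisation result. The form has no field for the rTMS target.

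**Analysis.** Section 11.2.2 gives paired t-tests for comparisons between groups and says that "repeated measures ANOVA will be used for intra-group comparisons". It names no covariate, stratum or subgroup.

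**Both diagnoses.** Section 3.1 admits GAD or MDD and nothing excludes having both. No section says which target rule then applies. Under Section 14.4 the treating researcher acts on the number in the opened envelope.

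**The concern.** The dual-target effect is an average over two stimulation regimens given to two kinds of patient, in a mix that is left to chance and not used in the stated analysis. With 22 patients per arm the mix can differ visibly between arms. If diagnosis is related to outcome, which is plausible at least for DASS-21, part of an observed contrast then reflects who was in the arm. A reader also cannot tell which regimen lies behind the dual-target result unless it is shown by diagnosis.

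The second issue concerns the variable itself. For a patient with both diagnoses the target has to be chosen by someone. If that happens after the envelope is opened, the category is no longer a baseline variable. A peripheral-arm patient never needs a target, so the category may not be recorded there at all. A covariate or by-diagnosis display built on it would then be defined differently across arms.

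**Working it through.** **1. Number per arm.** Section 5.1 states "under the conditions of β=0.1 and α=0.05, the effect size is 0.5" and that "there will be approximately 54 patients in the study cohort". Reading 0.5 as Cohen's f in a three-group one-way ANOVA (the type is not stated), the noncentrality is f² × N = 0.25 × 54 = 13.5 with 2 and 51 df, and power is 0.902. N = 51 gives 0.882. So 54 reproduces. The protocol then says "considering a 10% dropout rate, each group will include 22 people", and n = 22 is used below. (54/0.90 is 60, or 20 per arm, so 22 does not follow from 10% dropout. That is a separate matter.)

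**2. Assumptions not in the protocol.** The share p of one diagnosis is taken as 30-50%. The outcome gap g between diagnoses is taken as 0.5 SD, range 0.3-0.8 SD.

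**3. Chance imbalance.** The count with a given diagnosis in each arm is Binomial(22, p). Exact probabilities:

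| Difference | One given pair, p = 0.3 | One given pair, p = 0.5 | Most extreme of three pairs, p = 0.3 | Most extreme of three pairs, p = 0.5 |
|---|---|---|---|---|
| 5 or more of 22 (23 points) | 0.14 | 0.17 | 0.30 | 0.36 |
| 6 or more of 22 (27 points) | 0.07 | 0.10 | 0.16 | 0.22 |

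**4. Shift in the realised contrast.** Shift = (difference in counts / 22) × g. For a 5-patient difference:
- g = 0.3: 5/22 × 0.3 = 0.07 SD
- g = 0.5: 5/22 × 0.5 = 0.11 SD
- g = 0.8: 5/22 × 0.8 = 0.18 SD

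The standard error of a two-arm contrast in SD units is √(2/22) = 0.30.

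**5. Average over randomisations.** The expected shift is g × (p − p) = 0. Its SD at p = 0.5 and g = 0.5 is 0.5 × √(2 × 0.25/22) = 0.5 × 0.151 = 0.075. The contrast SD therefore rises from 0.30 to √(0.30² + 0.075²) ≈ 0.31. Simulation of an unadjusted two-sample comparison gives type I error of 0.049-0.050 for gaps up to 0.8 SD.

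**6. What adjustment gains.** Simulated power at a true effect of 1 SD, 22 per arm, p = 0.5:

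| Gap g | Unadjusted | Adjusted for diagnosis | Gain |
|---|---|---|---|
| 0 | 0.901 | 0.894 | −0.007 |
| 0.5 SD | 0.878 | 0.889 | 0.011 |
| 0.8 SD | 0.853 | 0.891 | 0.038 |

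A repeat of the 0.8 SD row with 400,000 simulated trials gives 0.853 to 0.893 at p = 0.5 and 0.861 to 0.893 at p = 0.3. The gains are 0.040 and 0.032, so about 0.035 is a fair summary over the assumed range.

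**7. The target rules side by side.** Section 6.1 item (3) and Section 6.2 send MDD patients to the left side and GAD patients to the right. Section 3.1 and the two lines on Appendix 7 allow both diagnoses in one patient. Such a patient satisfies both rules, and the rules give different answers. For a patient with one diagnosis the target follows automatically from what is recorded before allocation.

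**The case against.** The strongest case against has four parts.

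**No bias.** A reader might infer that leaving diagnosis out biases the arm contrasts or invalidates the tests. It does neither. Imbalance under valid randomisation is random error: the expected shift is zero and type I error holds at about 0.05. Even a 5-patient imbalance at a 0.5 SD gap shifts the estimate by little more than a third of its standard error (0.11/0.30). The 30-36% figure applies to the worst of three pairs, not to any contrast named in advance. All of this stands.

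**Unsupported inputs.** The protocol gives neither the diagnosis mix nor its relation to pelvic pain. This also stands. The reason that Section 5.2 gives for stratifying by gender plausibly extends to diagnosis for DASS-21, but nothing in the document shows that it does for the primary outcome.

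**Analysis plan and strata.** Covariates and subgroup displays are often set in a statistical analysis plan, which is not at hand, and with 66 patients it is reasonable to avoid more strata. The point about strata stands, and no extra stratum is asked for. The first part stands only partly. Section 11.2.2 states concrete methods without any covariate, and a later analysis plan cannot make the enrolment form capture the target before allocation.

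**A valid strategy.** Choosing the target by diagnosis is a legitimate individualised strategy whose average effect randomisation estimates, and diagnosis changes active stimulation in the dual-target arm only. This stands, so it would be too strong to say that the trial compares two different treatments in every arm. It does not remove the need to see that arm's result by diagnosis.

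**Conclusion.** The point holds as one of precision and interpretability, together with a gap in the target rules. A variable that selects the regimen, and is already collected before allocation, is not used in the stated analysis. The statistical cost is modest: adjustment raises power at a 1 SD effect by about 0.01 if the diagnosis gap is 0.5 SD and by about 0.035 if it is 0.8 SD. If there is no gap at all, adjustment loses about 0.007. These sizes rest on the assumed 30-50% share, the assumed gap and 22 patients per arm.

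The conflict between the target rules for patients with both diagnoses needs no assumption and follows from the text. How many patients it affects cannot be told from the protocol.

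**What to change.** 1. Keep randomisation stratified by sex only.
2. Include diagnosis, with sex and the baseline score, as a covariate in the between-arm model. This presupposes a stated model for comparing independent groups.
3. Show results by diagnosis descriptively, without subgroup tests.
4. The investigators must reconcile Section 6.1 item (3), Section 6.2 and the Plan Summary for patients who meet both diagnoses. Which target applies is for them to decide.
5. Add a line to Appendix 7 for the applicable target category, completed in all three arms before the envelope is opened.

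The cost is 1 degree of freedom, one line on an existing form and one descriptive table.
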